Measurements Activity 2: At T0, we will collect sociodemographic and data clinical from patients, including age, gender, sex, occupation, marital status, socioeconomic status and clinical diagnosis. We will also assess participants' expectations in the form of the question do you have any expectations regarding the use and efficacy of RVH? . At T0, T2 and T3, we will collect data on quality of life, anxiety, pain, fatigue and depression. The FACT-BMT is a validated scale for patients undergoing bone marrow transplantation. It contains 50 items divided into 5 subscales: Physical Well-Being, Social/Family Well-Being, Emotional Well-Being, Functional Well-Being and Bone Marrow Transplant Subscale on a 5-point Likert scale ranging from 0 = not at all to 4 = very much. The *Hospital Anxiety Depression Scale* (HADS) is a scale validated in French for cancer, which assesses participants' anxiety-depression. It is made up of 14 items: 7 items determine the degree of anxiety and the other 7, the degree of depression. The score of each subscale is calculated by summing the score of each item, which varies between 0 and 3, with each subscale reaching a maximum score of 21. Fatigue will be assessed using the 10-item version of the Multidimensional Fatigue Inventory (MFI-10) adapted to cancer. It is scored on a 5-point Likert scale ranging from 1: "strongly disagree" to 5: "strongly agree". Pain is assessed using the Brief Pain Inventory (BPI). This scale consists of 8 items on a 10-point Likert scale assessing pain severity, impact of pain on daily functions, location of pain, pain medication and extent of pain relief over the past 24 hours or week. At transplantation, we will use the diary with 11-level Scales before and after each RVH procedure to assess the direct effect of the procedure on pain, anxiety, enjoyment, i.e., the ability to enjoy oneself during the intervention, absorption, i.e., the tendency to become totally involved in a perceptual and imaginative experience, dissociation, i.e., a mental separation of components of the experience and fatigue. After each intervention, the Simulator Sickness Questionnaire, a scale validated in French, assesses symptoms of cybermalaise linked to immersion in VR. It contains 16 items divided into two subscales: nausea and oculomotor, which the participant must qualify as "not at all" (score 0), "a little" (score 1), "moderately" (score 2) or "severely" (score 3). . At T3, we will collect patients' level of satisfaction through a 19-item questionnaire that is evaluated on an 11-point Likert scale (0 = "strongly disagree" and 10 = "strongly agree" with the proposal). This questionnaire has been used in other studies to assess participant satisfaction with an intervention program^37. We will collect patients' levels of expectation and satisfaction using a five-level rating scale (1 = "not at all satisfied", 5 = "very satisfied") and explanatory interviews. Satisfaction interviews will also be conducted with caregivers in the hematology departments involved. The outcome secondary will be the change from T0 to T2 and T3 in the scores FACT-BMT, MFI and HADS-D, while the main outcomes primary will be changes from T0 in the degree of anxiety, of pain, . Changes in measures of pain, anxiety, amusement, absorption, and dissociation (logbooks completed during the two-week transplant stay) will also be considered secondary outcomes. We expect to At T3, we will assess acceptability and user experience with the User Questionnaire Experience (UEQ). This validated questionnaire is composed of 24 items that are evaluated on a 7-level Likert scale. It will be used to assess the six components of user experience: usability, usefulness, hedonic qualities (e.g., originality), attractiveness, sense of presence, resulting emotions. Sample size justification: At HMR, around 100 patients a year are treated for multiple myeloma and undergo cell transplantation stem. The sample size was also determined using a power calculation to ensure a sufficient probability of detecting a statistically significant effect, if any. We used an alpha significance level of 0.05 and a power (1 - B) of 0.95. The expected effect was estimated from \_\_\_\_\_, with an effect size of \_\_\_\_\_. Based on these

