
parameters, the power calculation suggests that a sample size of 60 participants is required to detect this effect with adequate power. The software \_\_\_\_ was used to perform this calculation. The sample size also takes into account a potential loss rate of \_\_\_\_%, to compensate for drop-outs and missing participants. .

Analyses Activity 1: The scores obtained on the questionnaire items will be compared with the theoretical mean of 6, i.e. the neutral level of acceptability on a scale from 0 to 10. An average above this threshold will be interpreted as a good experience of RVH. Analysis of the interview verbatim will enable us to make an open-ended assessment of the RVH experience. Significant narratives in each theme will be used to illustrate participants' opinions and experiences. Qualitative analysis of the narratives will enable us to identify positive and negative aspects, as well as avenues for improving the program. NVIVO software will be used for these analyses. This study will enable relevant modifications to be made to the program prior to the clinical effects study.

Analysis activity 2 :

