#### *Quantitative*

In order to evaluate the efficacy of the intervention in the experimental group compared to the control group, a MANCOVA will be performed. The dependent variables are anxiety, depression, pain, quality of life and fatigue, and the independent variables are the different measurement times. We will control for the following : gender, age, socioeconomic status, diagnosis, absorption, dissociation and enjoyment. We will make post-hoc comparisons to compare scores between groups and at each measurement time. They will be made with a correction covariates Bonferroni .

Correlations will be performed on variables measured during the transplant phase, to measure the immediate effects of RVH.

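### The immediate effect of RVH is to be measured by correlations, which cannot estimate the before-to-after change that the protocol declares as a secondary outcome

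*Protocol*

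**What the plan says.** Three parts of section 3 of the protocol (Methodologies) bear on this.

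- **Collection** (Measurements Activity 2). During the transplant stay, 11-level diary scales are completed "before and after each RVH procedure to assess the direct effect of the procedure on pain, anxiety, enjoyment", and also on absorption, dissociation and fatigue.
- **Outcome** (Measurements Activity 2). "Changes in measures of pain, anxiety, amusement, absorption, and dissociation (logbooks completed during the two-week transplant stay) will also be considered secondary outcomes".
- **Analysis** (Analysis activity 2, Quantitative). "Correlations will be performed on variables measured during the transplant phase, to measure the immediate effects of RVH". The type of correlation, the pairs of variables and the unit of analysis (patient or session) are not given.

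The other quantitative analysis is a MANCOVA of anxiety, depression, pain, quality of life and fatigue, intended to compare the experimental and control groups over the measurement times. The diary constructs absorption, dissociation and enjoyment enter it as control variables: "We will control for the following : gender, age, socioeconomic status, diagnosis, absorption, dissociation and enjoyment".

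**The concern.** The outcome is a change: how far a patient's pain or anxiety moves from just before a session to just after it. The analysis assigned to it is a measure of association. Association and mean change are different quantities, and one cannot be recovered from the other. Two variables can be strongly correlated with no average change, or weakly correlated with a large one.

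The diary is the protocol's source of before-and-after evidence for single sessions. If the analysis follows the text, the trial will hold paired ratings from about 30 RVH patients (60 randomised 1:1) and report coefficients that do not say whether patients felt better, worse or the same after a session. A sizeable pre-post coefficient would arise simply because some patients have more pain or anxiety than others throughout, and a reader told that correlations measure the immediate effect could take it for benefit.

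**Working it through.** **1. What is asked and what is named.** The collection and outcome texts ask for the mean of D = post - pre. The analysis text offers Corr(X, Y) for transplant-phase variables. The candidate pairings are these.

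*Pre with post.* For any constant c, Cov(pre, post + c) = Cov(pre, post) and SD(post + c) = SD(post), so Corr(pre, post + c) = Corr(pre, post). The coefficient is the same for every c. Rank correlations share this property, since adding a constant leaves ranks unchanged.

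*Change with another variable A (absorption, dissociation, enjoyment).* By the same algebra, Corr(A, D + c) = Corr(A, D). This tells whether patients with more absorption change more, not whether patients change on average.

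**2. Numerical illustration.** Thirty simulated patients, with pre ~ N(5, 2²) and post = 0.7 × pre + 1.5 + N(0, 1) + shift:

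| Shift | Pre-post r | Mean change |
|---|---|---|
| 0 | 0.754 | 0.01 |
| -1 | 0.754 | -0.99 |
| -2 | 0.754 | -1.99 |
| -3 | 0.754 | -2.99 |

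The value 0.754 belongs to this simulation; the invariance does not depend on it. On a real 11-level scale a shift may be cut off at the floor and r may then move, but that movement is still not an estimate of the mean change.

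**3. Does another planned analysis fill the gap?** The MANCOVA serves the group comparison over the study's measurement times. Its dependent variables come from the questionnaires collected at T0, T2 and T3. Absorption, dissociation and enjoyment appear in it only as control variables. It gives no session-level change.

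**4. Repeated sessions (conditional).** The diary recurs at each procedure, as does another form: "After each intervention, the Simulator Sickness Questionnaire". Several sessions per patient are therefore implied, but their number is not stated. If all sessions were pooled as independent and two variables were both clustered by patient, the variance of their correlation would be inflated by about 1 + (k - 1) × ICCx × ICCy. With k sessions and equal ICCs (both assumed):

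- k = 5, ICC 0.3: 1 + 4 × 0.09 = 1.36; square root 1.17
- k = 5, ICC 0.5: 1 + 4 × 0.25 = 2.00; square root 1.41
- k = 3, ICC 0.3: 1 + 2 × 0.09 = 1.18; square root 1.09
- k = 10, ICC 0.5: 1 + 9 × 0.25 = 3.25; square root 1.80

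Simulation with 30 patients agrees: standard-error ratios of 1.16 and 1.42 at k = 5, and 1.10 to 1.77 across k = 3 to 10. For two unrelated variables at nominal 5%, the type I error of a pooled correlation was 8.2% and 15.9% at k = 5 (ICC 0.3 and 0.5).

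The plan states no figure for this analysis, so there is none to reproduce.

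**The case against.** The strongest defence is that the sentence does not say pre-scores will be correlated with post-scores. Absorption, dissociation and enjoyment are also measured in the transplant phase, and relating them to change in pain or anxiety is a sensible use of correlation. The English is also visibly garbled in places, so one sentence should not be over-read, and a statistical analysis plan that is not shown may add detail. Much of this stands: a reader might infer that a pre-post coefficient will be presented as an effect, and the text does not establish that. It does not rescue the sentence, however. The stated purpose is to measure immediate effects, and neither pairing does so. This is a named method that does not fit a declared outcome, not a detail left for later.

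One pairing would respond to a shift: correlating the score with a before/after indicator. It amounts to an unpaired comparison, discards the pairing the diary was built to give, and is not described in the text.

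A reader might also infer that sessions will be treated as independent. The protocol does not say so; patient averages or a repeated-measures correlation would fit the wording equally well. Nor should the design effect for a mean, 1 + (k - 1) × ICC, be applied to a correlation. At k = 5 it gives 2.2 to 3.0, hence standard-error factors of 1.5 to 1.7, which overstate the effect on the method actually named.

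Finally, the primary outcomes are not touched: changes from T0 in anxiety and pain are addressed by the MANCOVA and its post-hoc comparisons.

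**Conclusion.** The point holds for the mismatch between outcome and method. A change in diary scores is declared as a secondary outcome, and correlations of the diary variables with one another, the only analysis named for it, cannot estimate a mean change. This follows from algebra and rests on no assumed value.

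The remark on repeated sessions is conditional. If sessions were pooled as independent, p-values would be too small, with the standard error of a correlation understated by a factor of about 1.2 to 1.4 at 5 sessions and ICC 0.3 to 0.5, or about 1.1 to 1.8 across 3 to 10 sessions. Session number and ICC are assumptions, and the pooling itself is not stated in the protocol.

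The weight is moderate: the outcome is secondary, and because the diary is tied to RVH procedures, the data appear to come from one arm only. It should be corrected before the diary data are analysed.

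**What to change.** Replace the sentence on correlations with an estimate of the mean within-session change, post minus pre or post adjusted for pre, for each diary measure declared as an outcome, with a 95% confidence interval. Either of two analyses would serve:

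- a linear mixed model with a random patient effect, with session number as an optional term; or
- a paired analysis of each patient's mean change. In simulation with 30 patients, 2 to 10 sessions and ICC 0.3 to 0.5, this kept type I error at 4.9% to 5.9%, against 9.5% to 41% for a test of mean change that pooled sessions as independent.

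State that the unit of inference is the patient. Label the result as an uncontrolled within-arm estimate, since no matching control ratings are described. Keep correlations only as exploratory analyses of absorption, dissociation or enjoyment against change.

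The cost is a change of wording and a little more analysis of data already planned. Collection and sample size are unaffected.

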#### *Qualitative*

The verbatims from the semi-structured interviews will be analyzed qualitatively using software NVivo . The software enables thematic content analysis, highlighting codes in the text and graphically grouping them into themes to create a thematic tree.

## **4. Benefits and expected results**

Expected results include the development and refinement of an RVH program in collaboration with clinicians, researchers, digital artists and patient partners. Members of our team (DO, PR, FR) have developed considerable expertise in this area, notably through studies on the effects of hypnosis, its effectiveness with cancer patients, and the design of RVH studies. The project also follows the development of a VR program by Super Splendid (JFM) to support palliative care patients, and a self-hypnosis (DO training ) developed with cancer patients. The involvement of partner patients (DW, SO) is also at the heart of this project. Involved at all stages of the research, patient partners and patient groups will bring their personal experience to bear, greatly enhancing the feasibility of the program, and hence its implementation in cancer clinics. Feasibility is also supported by the expertise of clinicians (RL, CD, AGA). HMR is a referral center for multiple myeloma in Canada, so we know this patient population well. Testing a program with such a sensitive population brings with it many challenges, such as managing significant side effects associated with treatments that could make it difficult to use VR, taking into account patients' immunosuppression and preventing infections. We have anticipated these challenges in the development of the program, in conjunction with advice from hematologists and patient partners and the ergonomic expertise of our collaborators, using, for example, VR hardware

specific to this hospital context, easy-to-use software interfaces and headset disinfection kits. All the data gathered in this project will be of prime importance in promoting this program with wider populations of oncology patients.

Important research prospects are also identified as a result of this project. Our research team includes several researchers in human neuroscience and physiological measurement (PR, KJ, PhR, ML) whose expertise is essential for studies complementary to our project. These studies will incorporate physiological measurements non-invasive of autonomic and brain activity to characterize responses to the intervention. These researchers are also involved in the development and evaluation of the intervention in a clinical context, to ensure that the experimental research protocols developed to assess neurophysiological mechanisms take account of the context of clinical applications. We anticipate that relevant complementary physiological measures will be incorporated into subsequent clinical studies

Following on from this project, we are planning multi-center efficacy studies with a wider population of cancer patients. To facilitate the opening up of this project to all cancer patients, an RVH user manual and a training program for healthcare staff are currently being developed, thanks to our collaborators: expert hypnosis training psychologists from Quebec, as well as collaborators from the University of Liège (ULG, Belgium) and Lille (France), involved in the tool development process thanks to their expertise in oncology hypnosis and RVH in clinical settings. All these steps will facilitate a multicenter randomized study with our collaborators (HMR, Sacré-Cœur, ULG, Université de Lille). The long-term objective is to propose the most effective, appropriate and comprehensive program for oncology patients, so that it can be used by a wide range of professionals (nurses, psychologists, educators, partners at the patient's bedside) and to extend this project to various centers cancer in the French-speaking world (Quebec, Belgium, France), in order to greatly improve ' quality of life. our patients

